**D. How much of the training was:**

|                 | 1. Some                  | 2. All                   | 3. None                  |
|-----------------|--------------------------|--------------------------|--------------------------|
| 1. New          |  |  |  |
| 2. Review       |  |  |  |
| 3. Not relevant |  |  |  |

**E. What was your most useful part of the training?**

---

---

**F. What was your least useful part of the training?**

---

---

**G. What are the facilitators to implement the knowledge from the training?**

---

---

---

---

**H. What are the barriers to implement the knowledge from this training?**

---

---

---

---

**J. Any other suggestion or comment to help us to improve the future training?**

---

---

---

---

**K. What, if anything, would you add to the training**

|  |
|--|
|  |
|  |
|  |
|  |

**Thank you very much for taking part in this research**

## 5.5 Appendix v: Checklist for auditing patients' records to be used with ICF checklist

One form will be completed for each patient record. Please place a sign ☒ in the box to indicate a positive response (only **one (1)** answer per statement).

| A. Informed consent                                                                                                            | Yes                      | No                       | N/A                      |
|--------------------------------------------------------------------------------------------------------------------------------|--------------------------|--------------------------|--------------------------|
| 1. The patient's consent is documented                                                                                         |  |  |  |
| 2. The patient's consent is signed                                                                                             |  |  |  |
| B. Patient's demographic information                                                                                    |                          |                          |                          |
| 3. Medical record number                                                                                                       |  |  |  |
| 4. Patient's name                                                                                                              |  |  |  |
| 5. Patient's gender                                                                                                            |  |  |  |
| 6. Date of birth/ Age                                                                                                          |  |  |  |
| 7. Address                                                                                                                     |  |  |  |
| 8. Marital status                                                                                                              |  |  |  |
| 9. Medical aid/No medical aid                                                                                                  |  |  |  |
| 10. Patient occupation                                                                                                         |  |  |  |
| 11. Level of education                                                                                                         |  |  |  |
| 12. Admit date                                                                                                                 |  |  |  |
| 13. Discharge date                                                                                                             |  |  |  |
| C. Comprehensive assessment                                                                                             |                          |                          |                          |
| 14. Health condition and diagnosis                                                                                             |  |  |  |
| 15. Symptoms                                                                                                                   |  |  |  |
| 16. Assessment of impairment                                                                                                   |  |  |  |
| 17. Impact of condition on functioning (Use ICF checklist. If yes, put the number of functioning addressed in the box).        |      |  |  |
| 18. Impact of environmental factors (Use ICF Checklist. If yes, put the number of Environmental factors addressed in the box). |      |  |  |
| D. Holistic intervention                                                                                                |                          |                          |                          |
| 19. Health condition managed in context                                                                                        |  |  |  |
| 20. Personal factors including mental and spiritual needs                                                                      |  |  |  |
| 21. Impairment addressed                                                                                                       |  |  |  |
| 22. Functioning addressed                                                                                                      |  |  |  |

|                                                                                                 |                          |                          |                          |
|-------------------------------------------------------------------------------------------------|--------------------------|--------------------------|--------------------------|
| 23. Environmental factors addressed                                                             |  |  |  |
| E. Continuum of care and discharge                                                       |                          |                          |                          |
| 24. Preventive measures of recurrence of health condition or complications related to condition |  |  |  |
| 25. Referral to other services                                                                  |  |  |  |
| 26. Discharge note                                                                              |  |  |  |
| F. Inter-professional practice                                                           |                          |                          |                          |
| 27. Referrals to other disciplines                                                              |  |  |  |
| 28. Case managed by different professionals                                                     |  |  |  |
| 29. Health professional team identified                                                         |  |  |  |
| 30. Health professionals treating the patient have documented                                   |  |  |  |

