## **2 Methodology – General**

### **2.1 Research setting**

The study will be carried out in Rwanda, specifically in district hospitals. Rwanda has 40 district hospitals covering four provinces plus four district hospitals in Kigali city (Government of Rwanda, MOH, 2013).

In general, apart from Kigali city, all district hospitals in Rwanda are similar in terms of patients and conditions, services, materials and equipment as well as health personnel, so the four hospitals from Kigali will not be part of this study. The district hospitals have both inpatient and outpatient services. Outpatient services include: general consultation, dentistry, laboratory, medical imaging, mental health, ophthalmology, HIV/AIDS unit, social welfare, and physiotherapy. Inpatient services includes: orthopaedic/surgical, medical, paediatrics, and maternity. This study will only recruit patients' records from inpatient services, specifically orthopaedic/surgical, internal medicine and paediatric. This choice is based on the fact that patients on these wards may be hospitalised for longer periods and receive treatment from different health professionals than those on other wards. The maternity ward will be excluded because the mothers generally spend only one to two days in hospital.

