##### **Patients' records**

- Medical records of patients who have been admitted to the orthopedic/surgical, medical and paediatric wards for at least five days.
- Medical records of patients who have been discharged.

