## 5.6 Appendix vi: International Classification of Functioning Disability and Health (ICF) checklist

One form will be completed for each patient record. Please place a sign ☒ in the box to indicate a positive response (only **one (1)** answer per statement).

| Activity Limitation & Participation Restriction                         |                          |                          |
|-------------------------------------------------------------------------|--------------------------|--------------------------|
| d1. LEARNING AND APPLYING KNOWLEDGE                                     | Yes                      | No                       |
| d110 Watching                                                           |  |  |
| d115 Listening                                                          |  |  |
| d140 Learning to read                                                   |  |  |
| d145 Learning to write                                                  |  |  |
| d150 Learning to calculate ( arithmetic )                        |  |  |
| d175 Solving problems                                                   |  |  |
| d2. GENERAL TASKS AND DEMANDS                                           |                          |                          |
| d210 Undertaking a single task                                          |  |  |
| d220 Undertaking multiple tasks                                         |  |  |
| d3. COMMUNICATION                                                       |                          |                          |
| d310 Communicating with -- receiving -- spoken messages                 |  |  |
| d315 Communicating with -- receiving -- non-verbal messages             |  |  |
| d330 Speaking                                                           |  |  |
| d335 Producing non-verbal messages                                      |  |  |

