| d820 School education                                                                 |  |  |
| d830 Higher education                                                                 |  |  |
| d850 Remunerative employment                                                          |  |  |
| d860 Basic economic transactions                                                      |  |  |
| d870 Economic self-sufficiency                                                        |  |  |
| d9. COMMUNITY, SOCIAL AND CIVIC LIFE                                                  |                          |                          |
| d910 Community Life                                                                   |  |  |
| d920 Recreation and leisure                                                           |  |  |
| d930 Religion and spirituality                                                        |  |  |

|                                            |                          |                          |
|--------------------------------------------|--------------------------|--------------------------|
| d940 Human rights                   |  |  |
| d950 Political life and citizenship |  |  |

| Environmental Factors                                                                       |                          |                          |
|---------------------------------------------------------------------------------------------|--------------------------|--------------------------|
| e1. PRODUCTS AND TECHNOLOGY                                                                 | Yes                      | No                       |
| e110 For personal consumption ( food, medicines )                                    |  |  |

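### Item 17 of the record audit is a raw count from one 48-item list for all ages, so the score partly reflects age and ward, and the analysis names neither.

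*Combined protocol and SAP*

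**What the plan says.** **Who is audited.** Section 2.1 limits the audit to inpatient records, "specifically orthopaedic/surgical, internal medicine and paediatric". Section 3.2.2.1 admits "Medical records of patients who have been admitted to the orthopedic/surgical, medical and paediatric wards for at least five days". Neither section sets an age limit.

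**What is recorded.** Item 17 of Appendix v instructs: "Use ICF checklist. If yes, put the number of functioning addressed in the box". Item 18 does the same for the environment: "put the number of Environmental factors addressed in the box". Neither gives a denominator. Both numbers are read from Appendix vi, which starts at "d1. LEARNING AND APPLYING KNOWLEDGE" and offers Yes and No only. That list includes adult-role items such as "Remunerative employment" and items suited to children such as "d140 Learning to read". Appendix v does have an N/A column, but at item 17 it applies to the item as a whole.

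**How it is used.** Section 3.2.2.2 makes record comprehensiveness, shown by scores, part of the primary outcome. It gives no rule for combining ticks, N/A answers and counts.

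**Ward mix.** Section 3.2.2.3 calls the sampling of records stratified but names no strata. Section 4 has the assistant audit every discharge until a hospital reaches 100.

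**Analysis.** Section 4.1 compares diagnosis categories between groups. It plans between-group t, Mann-Whitney or chi-square tests, within-group before/after tests, and a multi-level regression with no listed covariates. Ward and age do not appear.

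**The concern.** A raw count on a common list compares records fairly only if the list is equally open to every patient. It is not open in the same way to a toddler and to a working adult, so part of the variation in item 17 comes from who was admitted and not from how well staff documented. That has three consequences.

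- Where the paediatric share differs between hospitals, it adds between-hospital variance to a trial with only four hospitals per arm and a small expected effect (Section 3.2.2.2).
- Any comparison that ignores clustering can read a ward-mix difference as a difference in practice.
- A before/after comparison has no randomisation to protect it. Access to records changes between occasions: Sections 3.1.4 and 4.2 rely on the superintendent's permission at baseline, but on consent from patients or parents/guardians after training, and Section 4.2 adds assent from minors. This could move the paediatric share. The documents do not show that it would, or in which direction.

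**Working it through.** **1. The plan's own figures.** 0.20 × 40 = 8 hospitals; 8 × 100 = 800 records; 800 / 80 variables = 10 records per variable. These reproduce, but the point does not depend on them. No power calculation can be repeated, because the effect, SD, ICC, alpha and power are not given.

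**2. Length of the list (Appendix vi).**
- Functioning, d1 to d9: 6 + 2 + 5 + 6 + 7 + 4 + 7 + 6 + 5 = 48.
- Environment, e1 to e5: 6 + 3 + 7 + 7 + 9 = 32.

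**3. Items not applicable to a child, k (my judgement, shown as a range).**
- Low, k = 9: d475, d620, d630, d640, d770, d830, d850, d870, d950. Ceiling 48 − 9 = 39.
- High, for an infant, k = 25: those nine plus d140, d145, d150, d175, d220, d430, d470, d570, d660, d720, d740, d810, d820, d860, d910, d940. Ceiling 48 − 25 = 23.

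**4. Gap and false difference.** Assume a share f of applicable items is recorded at every age.
- Adult mean = 48f; adult-child gap = kf.
- If the paediatric share differs by Δ, the false difference is kfΔ, or kΔ/48 of the adult mean.

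| k | Δ = 0.10 | Δ = 0.20 |
|---|---|---|
| 9 | 9 × 0.10 / 48 = 1.9% | 3.75% |
| 25 | 25 × 0.10 / 48 = 5.2% | 10.4% |

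In items, the gap runs from 9 × 0.10 = 0.9 (f = 0.10) to 25 × 0.25 = 6.25 (f = 0.25). With Δ = 0.10 the false difference is 0.09 to 0.63 items.

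**5. Chance imbalance with 4 v 4 hospitals.** If the between-hospital SD of paediatric share is s (assumed), the arm difference has SD s × √(2/4).
- s = 0.10: 0.071, 95% range ±0.14.
- s = 0.15: 0.106, 95% range ±0.21.

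For s = 0.10, ward mix alone adds an SD of 0.9 × 0.071 = 0.06 to 6.25 × 0.071 = 0.44 items to the arm difference. This is the precision cost.

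**6. Null simulation.** Four v four hospitals, 100 records each, mean paediatric share 1/3, s = 0.10 to 0.15, f = 0.10 to 0.25, no training effect, 3,000 runs per setting. Type I error at nominal 5%:

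| Analysis | k = 9 | k = 25 |
|---|---|---|
| Unclustered t-test, raw count | 7% to 19% | 20% to 44% |
| Unclustered t-test, proportion of applicable items | 4.5% to 5.4% | 4.6% to 5.4% |
| t-test on hospital means, raw count | 5.1% to 5.8% | 4.6% to 6.2% |

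Ward mix is the only source of between-hospital variation in this simulation. The second row therefore shows that rescoring removes this source, not that unclustered tests are safe.

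**The case against.** Several objections have force.

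- **Item 17 can be marked N/A, and the list is not an adult list.** Both are true. But the N/A box covers the whole item and cannot adjust a count. As for the list, if adults are not expected to score the five learning and schooling items (d140, d145, d150, d810, d820), their practical ceiling is 43 and the gap to an older child is 43 − 39 = 4 items. That is 4/43 = 9%, or about 0.9% of the adult mean for each 10 points of ward mix. The problem is then small for school-age children and remains for infants and toddlers.
- **A lower ceiling is not a lower score.** This stands. A reader might infer that a child's record must score low. The documents do not support that, because the count depends on what staff write. If political life or higher education is rarely noted for any inpatient, the realised gap shrinks towards zero.
- **The raw count may not enter the primary score unscaled.** This also stands. If counts were simply added to the other 28 one-point items, items 17 and 18 could supply 80 of 108 points. Nothing in the plan says so, and nothing rules it out.
- **Randomisation and the multi-level model deal with ward mix.** They largely do so for chance imbalance in the main comparison: the test on hospital means held its level. They do not recover the lost precision, and they do not protect the other tests in Section 4.1.
- **The form is a draft.** Sections 2.2.3 and 3.1.4 leave it open to development and amendment. That makes the change easy, but no step in the plan addresses this issue.

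**Conclusion.** The point holds in limited form. As written, item 17 mixes documentation quality with age and ward. At equal completeness the distortion is about 2% to 5% of the adult mean count per 10 points of difference in paediatric share, and about 4% to 10% per 20 points. These figures rest on the judged range of 9 to 25 inapplicable items and on the equal-completeness assumption. Paediatric share and completeness are not given in the documents.

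In an analysis that respects the hospital as the unit of allocation, the main consequence is lost precision. A false difference is a risk in the unclustered between-group tests, and in the before/after tests if they are applied to the audit score; Section 4.1 does not say which outcome each test serves.

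A reader might go further and infer that ward mix biases the randomised comparison itself. The documents do not show this. Both arms use one list and hospitals are randomised, so systematic bias would need the ward mix to shift differently by arm after training, for example through consent or the 100-record cap. That is possible but not demonstrated.

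**What to change.** Keep paediatric records eligible and make these changes before the feasibility study ends.

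1. **Section 4.1:** include ward (surgical, medical, paediatric) as a fixed term in the multi-level model for the audit score.
2. **Section 3.2.2.3:** name ward as the sampling stratum, and reconcile this with the all-discharges rule in Section 4.
3. **Appendices v and vi:** score item 17 as the percentage of items applicable to the patient, using a short fixed list of items set to N/A by age band and settled in the feasibility study. Item 18 needs no age-based rescoring, since no environmental item has been shown to be inapplicable to children.
4. **Appendix v:** add fields for ward and age. As printed, the form has no ward field, and its age item only ticks whether age was recorded.

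Rescoring does not replace an analysis that accounts for clustering.

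The cost is one form revision and a few lines of text, with no new data source. Scores become percentages instead of counts. The N/A list must be agreed before rater agreement is tested against the 80% criterion (Sections 2.2.4 and 3.1.5); fixing it by age band keeps rater judgement out of it.

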## 5.6 Appendix vi: International Classification of Functioning Disability and Health (ICF) checklist

One form will be completed for each patient record. Please place a sign ☒ in the box to indicate a positive response (only **one (1)** answer per statement).

| Activity Limitation & Participation Restriction                         |                          |                          |
|-------------------------------------------------------------------------|--------------------------|--------------------------|
| d1. LEARNING AND APPLYING KNOWLEDGE                                     | Yes                      | No                       |
| d110 Watching                                                           |  |  |
| d115 Listening                                                          |  |  |
| d140 Learning to read                                                   |  |  |
| d145 Learning to write                                                  |  |  |
| d150 Learning to calculate ( arithmetic )                        |  |  |
| d175 Solving problems                                                   |  |  |
| d2. GENERAL TASKS AND DEMANDS                                           |                          |                          |
| d210 Undertaking a single task                                          |  |  |
| d220 Undertaking multiple tasks                                         |  |  |
| d3. COMMUNICATION                                                       |                          |                          |
| d310 Communicating with -- receiving -- spoken messages                 |  |  |
| d315 Communicating with -- receiving -- non-verbal messages             |  |  |
| d330 Speaking                                                           |  |  |
| d335 Producing non-verbal messages                                      |  |  |
| d350 Conversation                                                       |  |  |
| d4. MOBILITY                                                            |                          |                          |
| d430 Lifting and carrying objects                                       |  |  |
| d440 Fine hand use ( picking up, grasping )                      |  |  |
| d450 Walking                                                            |  |  |
| d465 Moving around using equipment ( wheelchair, skates, etc. )  |  |  |
| d470 Using transportation ( car, bus, train, plane, etc. )       |  |                          |
| d475 Driving ( riding bicycle and motorbike, driving car, etc. ) |  |  |
| d5. SELF CARE                                                           |                          |                          |
| d510 Washing oneself ( bathing, drying, washing hands, etc )     |  |  |

|                                                                                              |                          |                          |
|----------------------------------------------------------------------------------------------|--------------------------|--------------------------|
| d520 Caring for body parts ( brushing teeth, shaving, grooming, etc. )         |  |  |
| d530 Toileting                                                                        |  |  |
| d540 Dressing                                                                         |  |  |
| d550 Eating                                                                           |  |  |
| d560 Drinking                                                                         |  |  |
| d570 Looking after one`s health                                                       |  |  |
| d6. DOMESTIC LIFE                                                                     |                          |                          |
| d620 Acquisition of goods and services ( shopping, etc. )                      |  |  |
| d630 Preparation of meals ( cooking etc. )                                     |  |  |
| d640 Doing housework ( cleaning house, washing dishes laundry, ironing, etc. ) |  |  |
| d660 Assisting others                                                                 |  |  |
| d7. INTERPERSONAL INTERACTIONS AND RELATIONSHIPS                                      |                          |                          |
| d710 Basic interpersonal interactions                                                 |  |  |
| d720 Complex interpersonal interactions                                               |  |  |
| d730 Relating with strangers                                                          |  |  |
| d740 Formal relationships                                                             |  |  |
| d750 Informal social relationships                                                    |  |  |
| d760 Family relationships                                                             |  |  |
| d770 Intimate relationships                                                           |  |  |
| d8. MAJOR LIFE AREAS                                                                  |                          |                          |
| d810 Informal education                                                               |  |  |
| d820 School education                                                                 |  |  |
| d830 Higher education                                                                 |  |  |
| d850 Remunerative employment                                                          |  |  |
| d860 Basic economic transactions                                                      |  |  |
| d870 Economic self-sufficiency                                                        |  |  |
| d9. COMMUNITY, SOCIAL AND CIVIC LIFE                                                  |                          |                          |
| d910 Community Life                                                                   |  |  |
| d920 Recreation and leisure                                                           |  |  |
| d930 Religion and spirituality                                                        |  |  |

|                                            |                          |                          |
|--------------------------------------------|--------------------------|--------------------------|
| d940 Human rights                   |  |  |
| d950 Political life and citizenship |  |  |

| Environmental Factors                                                                       |                          |                          |
|---------------------------------------------------------------------------------------------|--------------------------|--------------------------|
| e1. PRODUCTS AND TECHNOLOGY                                                                 | Yes                      | No                       |
| e110 For personal consumption ( food, medicines )                                    |  |  |
| e115 For personal use in daily living                                                       |  |  |
| e120 For personal indoor and outdoor mobility and transportation                            |  |  |
| e125 Products for communication                                                             |  |  |
| e150 Design, construction and building products and technology of buildings for public use  |  |  |
| e155 Design, construction and building products and technology of buildings for private use |  |  |
| e2. NATURAL ENVIRONMENT AND HUMAN MADE CHANGES TO ENVIRONMENT                               |                          |                          |
| e225 Climate                                                                                |  |  |
| e240 Light                                                                                  |  |  |
| e250 Sound                                                                                  |  |  |
| e3. SUPPORT AND RELATIONSHIPS                                                               |                          |                          |
| e310 Immediate family                                                                       |  |  |
| e320 Friends                                                                                |  |  |
| e325 Acquaintances, peers, colleagues, neighbours and community members                     |  |  |
| e330 People in position of authority                                                        |  |  |
| e340 Personal care providers and personal assistants                                        |  |  |
| e355 Health professionals                                                                   |  |  |
| e360 Health related professionals                                                           |  |  |
| e4. ATTITUDES                                                                               |                          |                          |
| e410 Individual attitudes of immediate family members                                       |  |  |
| e420 Individual attitudes of friends                                                        |  |  |
| e440 Individual attitudes of personal care providers and personal assistants                |  |  |
| e450 Individual attitudes of health professionals                                           |  |  |
| e455 Individual attitudes of health related professionals                                   |  |  |

|                                                                   |                          |                          |
|-------------------------------------------------------------------|--------------------------|--------------------------|
| e460 Societal attitudes                                    |  |  |
| e465 Social norms, practices and ideologies                |  |  |
| E5. SERVICES, SYSTEMS AND POLICIES                         |                          |                          |
| e525 Housing services, systems and policies                |  |  |
| e535 Communication services, systems and policies          |  |  |
| e540 Transportation services, systems and policies         |  |  |
| e550 Legal services, systems and policies                  |  |  |
| e570 Social security, services, systems and policies       |  |  |
| e575 General social support services, systems and policies |  |  |
| e580 Health services, systems and policies                 |  |  |
| e585 Education and training services, systems and policies |  |  |
| e590 Labour and employment services, systems and policies  |  |  |

